### 7.1. Aims

The ultimate goal of the proposed study is to mitigate COVID-19 risk in HK communities. Objective 1: To equip community partners with the knowledge and skills necessary to design and implement appropriate interventions for COVID-19 prevention. Objective 2: To carry out community-based education programmes for improving early testing for COVID-19, increasing vaccination rate and enhancing self-protection measures against COVID-19 in HK. Objective 3: To determine the most sustainable and suitable community education model and use it on a large scale across different communities. 

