### 7.2. Plan of Investigation

A 4-year community-based health education project known as ‘AID (Assistance, Improvement, Development)’ will be implemented. The project will have four stages. Stage 1 and stage 2 are community mobilisation stages. Stage 1 will involve academic–community team building through administrative processes. Stages 2 is capacity building stage that mobilize the partners to enhance their ability for conducting community programmes. Stage 3 will involve the design and implementation of the interventions using a cluster randomised controlled trial (RCT), and Stage 4 will be the model-enhancing stage, in which the achievements and experiences from the previous three stages will be summarised and disseminated to the wider public.

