Sample size: As a cluster RCT, the randomization is conducted in the cluster level. In our study, each cluster is a group of participants recruited by the same research partner. In our study, based on our simulation modelling [32], a 20% increase in the vaccination rate could have significant social benefit. With conventional assumptions of a two-sided 5% significance level and assuming an intra-cluster correlation of 0.01, we would have 86% power to detect a difference of 20% if there are 50 participants in each cluster and 8 clusters in each sector [33]. Thereby 3 sectors will have 3 × 8 = 24 clusters and 1200 participants in total. For each sector, 8 clusters (400 participants) will be evenly divided into either the intervention group or the control group. When we used the same method to calculate the sample size for detecting 20% difference in the percentage of early testing (another primary outcome), the sample size was smaller than the previous one. We thereby consider the former one as our final sample size, as it could ensure the power of the study.

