##### Stage 3: Implementing the Community-Based Health Education Programmes

Design and setting: stage 3 is a multicentre cluster RCT. The intervention programmes will be implemented by the research partners. 

Randomisation and concealment: The participants recruited by one research partner will be considered as one cluster. A research assistant will randomly assign the clusters from the NGOs, Schools, and Companies to either the intervention group or the control group, respectively. Concealment of the allocation sequence to the investigators will be done until assignment occurs. After allocation, there will be four clusters in both the intervention and control groups from the NGOs, schools and companies, respectively. This will result in 3 × 4 = 12 clusters for each group (intervention/control). An active wait-list control group will be used instead of a standard control group to help motivate the collaborators to implement the programme and to avoid a high participant dropout rate. Intervention: The core intervention package will potentially include the following four components. (1) A manual of self-protection against COVID-19 infection. The main content will include hand washing, mask wearing and social distancing guidelines. (2) Early testing. Participants will be trained on how to recognize the early symptoms of COVID-19 and appropriate practice to take in a response, and they will be provided with testing resources. The COVID-19 Rapid Antigen Test (RAT) will be provided to participants as an incentive to facilitate self-testing at home. This RAT is a lateral-flow immunoassay designed for the qualitative detection of SARS-CoV-2 antigens in nasal swab samples. (3) Knowledge of vaccines and their benefits and resources for vaccination. (4) Post-vaccination follow-up. Participants will be trained on how to recognise vaccine side effects and to provide further protection measures, and they will be provided with resources for consultation and treatment. The research partners will design the community-based education programmes (based on the core intervention) after the TTT workshop. They will be required to submit a brief standardized proposal to the academic investigators for review and approval, to ensure that all intervention programmes have the same core intervention contents and can be implemented appropriately. The development and implementation of the intervention will follow the procedures outlined in the PROCEDE-PROCEED model (Figure 2). Research partners will be able to use any reasonable strategies, such as social media platforms, information technology, posters, leaflets, and videos, to implement the programmes. Each programme will last for 3 months. The active wait-list control group will undergo parallel assessment at the same time points as the intervention group, while the core intervention contents will be delivered after 3 months. We expect that the 24 intervention programmes will be completed within 2 years. Evaluation: Evaluations will be conducted at baseline (T_0_), middle term (T_1_, 1.5 months), and at the end of the trial (T_2_, 3 months). Participants’ knowledge, attitudes and behaviours towards COVID-19 prevention will be evaluated using a self-designed questionnaire, based on the KAP model. In addition, a process evaluation that determines whether the programme is being implemented as intended will be performed as follows. Every month, the academic investigators and the collaborators will review the progress of each programme together. Information on the attendance rate of each programme and feedback from program participants and research partners will also be evaluated qualitatively. A flow chart of the all the data collection steps is shown in Figure 3.

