
##### Stage 4: Health education model enhancement and promotion

An agent-based simulation model that considers human mobility in HK will be developed [36]. The model will be trained using data from the 24 community-based intervention programmes, to establish the most optimal community-based health education model(s) for COVID-19 prevention. We assume different intervention programmes will cause different changes in the vaccine uptake patterns among participants. Each intervention programme’s result (e.g., the vaccine uptake number) will be collected for comparison purposes. Then, the programme with maximal vaccine uptake and minimal healthcare requirements (e.g., number of infections detected) will be chosen as the most optimal strategy. Once the simulation modelling is completed, a toolkit book that contains (1) training workshop content and (2) details on the implementation and assessment of the most optimal health education model(s) will be produced and disseminated to additional NGOs, companies and schools. A health education pamphlet containing relevant COVID-19 information and the successful experiences of our health education programmes will be disseminated to the public via the research partners within one year. We expect that 200 NGOs, companies and schools will be approached, and 20,000 HK residents will receive the pamphlets. In addition, several press conferences will be held to share our findings and experiences with the public.

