#### 10.2.2. Study Methods

Our study will be conducted in three stages. In Stage 1, we will perform an exploratory sequential mixed-methods study with an online survey followed by an exploratory qualitative study. In Stage 2, we will conduct an RCT to test the efficacy of the ‘AI-driven Vaccine Communicator’ relative to being self-informed about COVID-19 vaccines. In Stage 3, after the RCT (Stage 2), we will adopt and implement the intervention as a service evaluation to a wider HK population.

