## 12. Across All Studies, Other Common Elements Include

Stop-and-go criteria [39] will be used in terms of subject recruitment (<20% vs. >50% meeting eligibility criteria, respectively); intervention acceptability (<30% vs. >60 or >70%, respectively, in different studies), and loss to follow up (<30% vs. >70 or >80%, respectively, in different studies). Furthermore, the RE-AIM framework [61] will be used to guide the evaluation of all studies. We will collect metrics on Reach (e.g., number of website visits), Effectiveness (changes in stay-at-home motivation and intention or changes in hygiene practice), Adoption (e.g., the amount of content created by the public with the campaign hashtag), Implementation (e.g., consistency in implementation of the educational VRG), and Maintenance (e.g., number website visits after the programme) as appropriate, to document formative and summative impact. All analyses will be performed using SPSS 26.0 software and a *p* value < 0.05 will be considered statistically significant.

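### Study 1, Stage 4 names an optimal programme by ranking programmes against each other and never uses the randomised comparison with control

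*Protocol article*

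**What the plan says.** Objective 3 of Study 1 (section 7.1, Aims) is to find the most suitable "community education model and use it on a large scale across different communities". Section 7.2 gives the outline: "Stage 4 will be the model-enhancing stage, in which the achievements and experiences from the previous three stages will be summarised and disseminated".

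The operative text is under Stage 4 in section 7.2.2. An agent-based simulation model is trained on data from the 24 community programmes. The programme with the most vaccine uptake and the least healthcare requirement is selected and labelled optimal. When the modelling ends, a toolkit describing that model goes to further organisations. In addition, "A health education pamphlet containing relevant COVID-19 information and the successful experiences of our health education programmes will be disseminated to the public". About 200 organisations are to be approached, and 20,000 residents are to receive the pamphlet.

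The randomised evidence is described elsewhere. Under Stage 3, "there will be four clusters in both the intervention and control groups from the NGOs, schools and companies, respectively", which makes 12 v 12 clusters overall. Section 7.2.3 plans an intention-to-treat comparison between the groups.

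Section 12 sets go/no-go rules for all five studies: "Stop-and-go criteria [39] will be used in terms of subject recruitment", with intervention acceptability and loss to follow-up as the other two. Effectiveness is not among them.

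**The concern.** Two questions need separate answers: which programme did best, and whether the intervention works at all. The Stage 4 rule answers only the first. All programmes must carry the same core content (Stage 3 text), so comparing them with each other cannot show whether that core raises uptake. Only the comparison with the wait-list control can, and Stage 4 does not refer to it.

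At stake is an unsupported conclusion. After a null or unfavourable trial, the plan as written would still produce a model called optimal and a public account of success.

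A null result on vaccination is not remote. The Introduction reports 84.3% two-dose coverage. Study 1 does not restrict entry to unvaccinated people. If participants resembled the general population and the outcome counted two doses (both are assumptions, as the article does not state them), at most 100 − 84.3 = 15.7 points of gain would be available against a target of 20.

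**Working it through.** **1. The plan's own figure.** Section 7.2.1 uses a "two-sided 5% significance level and assuming an intra-cluster correlation of 0.01" and states that "we would have 86% power to detect a difference of 20% if there are 50 participants in each cluster and 8 clusters in each sector".
- Design effect: 1 + (50 − 1) × 0.01 = 1.49.
- Effective size per arm per sector: 4 × 50 / 1.49 = 134.2.
- The control rate is not given, so it was varied. A z-test gives 91 to 92% power for 30 v 50%, 37 v 57%, 40 v 60% and 50 v 70%, and 95% for 60 v 80%.
- A t-test with 6 degrees of freedom gives 80 to 81% for the first four pairs and 86.0% for 60 v 80%.

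So 86% is attainable but not fixed by the stated inputs. Nothing below depends on it.

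**2. What the rule uses.**

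| Step | Input used | Comparison with control? |
|---|---|---|
| Train the simulation model | Data from 24 programmes | None stated |
| Choose the optimal programme | Uptake and healthcare requirements, between programmes | None stated |
| Issue the toolkit | Completion of the modelling | None stated |
| Pamphlet content | Successful experiences | None stated |
| Stop-and-go (section 12) | Recruitment, acceptability, loss to follow-up | None stated |

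Twelve of the 24 programmes are wait-list deliveries, given after the 3-month randomised comparison and so without a concurrent control.

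**3. What a ranking shows when nothing differs.** Assume K programmes of 50 people with the same true uptake p and intra-cluster correlation ρ.
- Draw each programme's rate from Beta[p(1 − ρ)/ρ, (1 − p)(1 − ρ)/ρ].
- Draw uptake from Binomial(50, rate).
- Take the largest observed proportion minus p. There were 100,000 runs.

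| K | ρ | Assumed p | Mean excess of the top programme | Chance it looks ≥ 20 points better |
|---|---|---|---|---|
| 24 | 0.01 | 37–60% | 15.9–16.7 points | 20.5–28.1% |
| 12 | 0.01 | 37–60% | 13.4–14.0 points | 10.7–15.2% |
| 24 | 0.05 | 37–60% | 23.2–25.8 points | 80.2–85.5% |
| 24 | 0.01 | 84% | 10.7 points | 0 (ceiling) |

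Plausibility check at p = 50%, ρ = 0.01: the SD of one programme's proportion is √(0.25 × 1.49 / 50) = 0.0863. The simulated excess of 0.167 is 0.167 / 0.0863 = 1.9 SDs, a reasonable size for the largest of 24 draws.

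The ranking here uses uptake alone. The healthcare criterion has no stated weight and was not modelled.

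**4. What the unused contrast could show.** With 12 × 50 / 1.49 = 402.7 effective participants per arm, a normal-approximation test from 40% has 81.5% power for a 10-point difference, against 37.6% within one sector. The pooled comparison is informative enough to be worth using.

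**The case against.** **Silence in a condensed article.** The article covers five studies, and a rule on post-trial dissemination might sit in a fuller document. That would answer a complaint that a rule is missing. Here a rule is printed, with its selection criterion, its trigger and the tone of the message, and that rule leaves out the trial result.

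**Effectiveness is not ignored.** Section 12 also adopts RE-AIM, which includes effectiveness. Section 7.2.3 plans the between-group analysis, and Stage 4 promises press conferences on the findings. All true, but none of these is linked to the optimal label or to the pamphlet message.

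**The outline sentence is harmless.** The sentence quoted from section 7.2 only announces summary and dissemination, which is unobjectionable. The problem lies in the Stage 4 text.

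**Little direct harm.** The core content is hygiene, testing and vaccine information. The 20,000 people receive pamphlets and the 200 organisations are approached; neither figure counts people given the selected programme. This stands: the cost is a misleading claim, not a hazard from the material.

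**Stronger readings that the article does not support.**
- A reader might infer that the investigators intend to scale up whatever the trial shows. The article never says so; this is only a consequence of unconditional wording.
- A reader might see the same fault in Study 4, where "In Stage 3, after the RCT (Stage 2), we will adopt and implement the intervention as a service evaluation to a wider HK population". That stage is a service evaluation with effectiveness as one of five components. It makes no selection among programmes and applies no optimal label.
- A reader might want all dissemination withheld unless vaccination improves significantly. Objective 2 also covers early testing and self-protection, and section 7.2.1 calls early testing another primary outcome. Such a gate could block a model that helped in other ways.

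**Conclusion.** The point holds for Study 1, Stage 4, as a matter of decision logic. By construction the rule always returns a top programme, and no step makes the optimal or successful label depend on the randomised comparison. This needs no numerical assumption.

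The simulation only shows why a ranking cannot stand in for that comparison: chance alone gives the leader an apparent advantage close to the plan's 20-point target. It rests on equal true uptake, 50 people per programme, an assumed uptake of 37 to 60%, and the plan's correlation of 0.01. The advantage is smaller near the ceiling and larger at a correlation of 0.05. No probability of wrongly scaling up is claimed, because such a figure would only restate whichever rule is assumed.

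**What to change.** Change the Stage 4 text in section 7.2.2 as follows.

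1. State that a model is described as optimal or effective only where the randomised intervention-versus-control estimate, with its cluster-adjusted 95% CI, supports a benefit on the outcome being claimed (vaccination or early testing).
2. State that otherwise the toolkit and pamphlet may still share general COVID-19 information, but must carry the trial estimate and say that the programme was not shown to improve that outcome.
3. Replace the reference to successful experiences with the results of all programmes, including null ones.

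This is a wording change, with no extra participants or data. The cost is that, after a null trial, the promotional message becomes a report of results.

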#### 7.2.1. Subjects

In accordance with the CBPR approach, two kinds of people will be involved in our project: research partners and study participants. Research partners will help to recruit study participants. The study participants will be land-based non-institutional HK residents. Three types of participants will be recruited: adults from the general population, high-exposure groups, and middle school students and their parents. General adults are the majority of the HK population, their responses and feedbacks to the health education programme are representative and important. The high-exposure groups will consist of those more frequently exposed to the virus, such as truck, taxi and bus drivers; fitness instructors; restaurant waiters; and employees of cold-chain logistics companies. These individuals may have a higher risk of being in contact with virus carriers, becoming infected and transmitting the virus to other people. School students are another target group requiring particular attention for infection protection, and their parents will also be involved in the project. With these considerations, we will choose research partners in three main sectors: (1) local community NGOs, (2) company and business employers and (3) teachers in middle and high schools. Sector in this study means the organization that we target to collaborate with. The research partners will be invited from these sectors. Research partners from these sectors will help in the recruitment of participants and expediently carry out the intervention programmes. For participants recruited in sectors (1) and (2), the inclusion criteria will be: (1) HK residents aged 18 years or above and (2) agreement to participate in the study and provide written informed consent. Participants in sector (3) will consist of students aged 12 to 18 years, studying in public secondary schools in HK, and their parents. Those who cannot provide written informed consent (or assent for the younger students) will be excluded from the study. 

Sample size: As a cluster RCT, the randomization is conducted in the cluster level. In our study, each cluster is a group of participants recruited by the same research partner. In our study, based on our simulation modelling [32], a 20% increase in the vaccination rate could have significant social benefit. With conventional assumptions of a two-sided 5% significance level and assuming an intra-cluster correlation of 0.01, we would have 86% power to detect a difference of 20% if there are 50 participants in each cluster and 8 clusters in each sector [33]. Thereby 3 sectors will have 3 × 8 = 24 clusters and 1200 participants in total. For each sector, 8 clusters (400 participants) will be evenly divided into either the intervention group or the control group. When we used the same method to calculate the sample size for detecting 20% difference in the percentage of early testing (another primary outcome), the sample size was smaller than the previous one. We thereby consider the former one as our final sample size, as it could ensure the power of the study.

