During Stage 2, quantitative data from the pre- and post-programme evaluations will be analysed using a paired Student’s *t*-test for continuous variables and McNemar’s test for categorical variables. Qualitative data from the focus group interviews will be first organised by an experienced qualitative researcher. The transcripts will be coded and analysed in a systematic and iterative manner. Finally, themes and subthemes will be generated. During Stage 3, cluster RCT data will be analysed according to an intention-to-treat (ITT) principle. All participants who attend baseline assessment will be included in the ITT analysis. Within groups, changes at T_1_ and T_2_ time points will be compared with baseline (T_0_) data using a paired Student’s *t*-test or McNemar’s test, as appropriate. To compare the between-group differences in mean change from baseline to 3 months, as well as testing the time × group interaction effects between groups, linear mixed models will be adopted for analyses. The variables that are significantly different between groups at baseline will be used as covariates in the linear mixed models. Binary logistic regression models will be also used to examine the association between interventions and the main outcomes. Odds ratios will be calculated to determine the magnitude of the intervention effect.

## 8. Study 2

Digital Health Literacy on COVID-19 for All: Co-creation and evaluation of interventions for ethnic minorities and Chinese people with chronic illnesses in Hong Kong

This is the first DHL intervention to be developed with a community-based participatory research approach [37] and to be co-created with the stakeholders. It is essential to build up everyone’s capacity to access, understand and interpret the health information they receive and to make appropriate health decisions (i.e., DHL). Once they learn the skills or improve their ability to search for reliable health information and evaluate it in a critical manner, they can apply such skills and abilities to other health issues.

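### Study 1's 86% power is for one sector (4 v 4 clusters), but the planned comparison is intervention v control over 12 v 12 clusters, with no term for the sector within which clusters are randomised

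*Protocol article*

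**What the plan says.** All references are to Study 1 in the Protocol article.

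- **Sizing (7.2.1 Subjects).** The assumptions are introduced as "With conventional assumptions of a two-sided 5% significance level and assuming an intra-cluster correlation of 0.01", and the result is "86% power to detect a difference of 20% if there are 50 participants in each cluster and 8 clusters in each sector". The total follows by multiplication: "Thereby 3 sectors will have 3 × 8 = 24 clusters and 1200 participants in total". Within a sector, "For each sector, 8 clusters (400 participants) will be evenly divided into either the intervention group or the control group", which is 4 v 4 clusters. No control-arm vaccination rate is given.
- **Randomisation (Stage 3).** A research assistant will "randomly assign the clusters from the NGOs, Schools, and Companies to either the intervention group or the control group, respectively", so allocation is done separately within each sector. The arms are then added up across sectors: "This will result in 3 × 4 = 12 clusters for each group (intervention/control").
- **Analysis (7.2.3).** Vaccination rate is primary. Linear mixed models are to be used "To compare the between-group differences in mean change from baseline to 3 months", and logistic regression is to relate the main outcomes to intervention. Covariates in the mixed models are those found to differ significantly between groups at baseline. Sector appears neither as a factor nor as the basis of a separate test.
- **Threshold (section 12).** p < 0.05 is used throughout.

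**The concern.** The sizing and the analysis describe different comparisons. The sizing treats each sector as a self-contained 4 v 4 comparison and triples it. The analysis describes one contrast between two groups, and the only definition of those groups is 12 v 12 clusters.

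Two things are at stake:

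- A reader will take 86% as the power of the trial's main test for a 20-point difference. If it is not, the document does not say what difference the main test can detect, and a significant result could rest on an effect well below the 20% that 7.2.1 calls socially important.
- The randomisation is stratified by sector but the model is not. The three sectors are different populations (adults reached through NGOs, employees in high-exposure work, and students with their parents), so their vaccination rates may differ. A model that ignores the stratification counts those differences as noise between clusters.

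**Working it through.** **Inputs from 7.2.1 and Stage 3:** two-sided alpha 0.05; ICC 0.01; m = 50 per cluster; difference 20%, read as 20 percentage points; k = 4 clusters per arm in a sector; k = 12 per arm across sectors.

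**Assumption:** the control rate p0 is not stated, so 20% to 60% is used. The calculation method is in a cited source that is not shown.

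**Formulae**

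- Design effect = 1 + (50 − 1) × 0.01 = 1.49.
- Effective n per arm = 50k / 1.49, which is 134.2 for k = 4, 268.5 for k = 8 and 402.7 for k = 12.
- SE = √[(p0(1 − p0) + p1(1 − p1)) / effective n], with p1 = p0 + 0.20.
- Power from the noncentral t distribution with 2k − 2 df and noncentrality 0.20 / SE.

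**The plan's 86%.** Take 20% v 40% with k = 4. The variance sum is 0.16 + 0.24 = 0.40, SE = √(0.40 / 134.2) = 0.0546, noncentrality = 3.66, critical t on 6 df = 2.447, and power = 86.0%. By symmetry 60% v 80% gives the same. At 40% v 60%, SE = √(0.48 / 134.2) = 0.0598, noncentrality = 3.34 and power = 79.5%.

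| Clusters per arm | df | Power for 20 points, p0 from 20% to 60% |
|---|---|---|
| 4 (one sector) | 6 | 79% to 86% |
| 8 | 14 | over 99% |
| 12 (all sectors) | 22 | over 99.9% |

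Other methods for 4 v 4 over the same control rates give 91% to 95% (plain normal approximation), 89% to 94% (continuity-corrected) and 83% to 89% (normal, one cluster per arm deducted). The 86% is thus compatible with 4 v 4 under some methods and rates, and not with 8 v 8 or 12 v 12. It cannot be strictly reproduced without the control rate.

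**What 12 v 12 can detect.** With 22 df, the difference that gives 86% power is 9.6 points at p0 = 20%, 11.1 at 40% and 10.6 at 60%. That is about 10 to 11 points, roughly half of the 20 in the sizing.

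**Sector in the model.** After allocation each arm has 4 clusters from each of the three sectors. With equal cluster sizes, sector has the same distribution in both arms, so a baseline test cannot show it as different and the covariate rule in 7.2.3 will not select it. Under the design assumptions the variance of a cluster's rate is p(1 − p) × 1.49 / 50. If sector is left out, the variance of the sector rates is added to this in the estimated error. The estimated effect stays balanced, but its standard error is too large. The size cannot be computed, because no sector-specific rates are given.

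**The case against.** The strongest reply is that the mismatch does no harm to error control. Intervention v control is the only between-arm contrast written, there is one such contrast for vaccination rate, and it is tested at 5%. Sizing each sector to give a useful estimate and then analysing by arm is legitimate and errs on the side of too much power. Model detail is also commonly left to an analysis plan. All of this stands as far as false-positive risk and sample size are concerned.

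It also disposes of a stronger reading that the per-sector sizing invites. A reader might infer three sector tests at 5% each, with a family-wise error of 1 − 0.95³ = 14.3% if any one counts as success, or a power of 0.86³ = 64% if all three must succeed. The document plans no sector test, no any-sector rule and no all-sector rule. Those figures say what would follow if sector tests decided the trial; they do not describe this plan.

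The reply does not remove two points. The power given in the document is not that of the comparison in the document, which is a mismatch between two stated items and not an omitted detail. And 7.2.3 does fix a covariate rule, one that cannot admit the stratification factor.

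**Conclusion.** The point holds as a mismatch between sizing and analysis. By its wording, and by calculation, 86% belongs to one sector's 4 v 4 comparison. The planned intervention v control comparison over 12 v 12 clusters has over 99.9% power for 20 points and can detect about 10 to 11 points at 86%. These figures rest on the plan's ICC of 0.01 and 50 per cluster, on reading 20% as percentage points, and on assumed control rates of 20% to 60%. They also ignore any loss of precision from leaving sector out.

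Reading the groups as all 24 clusters together is an inference from the 12-cluster count in Stage 3, since 7.2.3 does not say so outright; it is the only definition of the groups given. The documents do not support a claim of inflated type I error or of an underpowered trial. The consequences are a mis-stated power and, if sector rates differ, a standard error larger than it needs to be.

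**What to change.** In 7.2.1 and 7.2.3:

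1. Name the 3-month intervention v control comparison of vaccination rate over all 24 clusters as the primary test, at two-sided 5%, with sector as a fixed (stratification) factor whatever the baseline tests show.
2. State the power or detectable difference of that test, together with the assumed control rate.
3. Label 86% as the power within one sector.
4. Report sector-specific results as secondary.

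The cost is wording only. The 24 clusters and 1200 participants stay as they are. The downside is that claims about a single sector become secondary. If the intention was in fact to judge each sector separately, the document would have to say so and give the success rule and any split of alpha.
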